### Data collection

Informed consent to participate in the study was given by a parent, guardian or participant (if of suitable age and understanding) and assent was granted by younger participants. Each participant received study equipment (table 1, figure 2), to record and synchronise data, and was issued a unique anonymous Microsoft login account with a strong password (managed by the study team) for logging into the tablet, Fitbit app (Fitbit) and bespoke Fizzyo app. A researcher demonstrated how to use the equipment to participants. These instructions and technical support contact details were provided as a printout and webpage link via QR code.

**Table 1 T1:** Study equipment for participants

	ACT sensor	Activity tracker	Tablet computer
**Description**	Bespoke Fizzyo Sensor. Wireless battery powered pressure sensor that attaches to ACT devices to measure pressure during ACT.	Fitbit Alta HR. Wrist-worn activity tracker with heart rate sensor to record daily physical activity.	Linx 12X64 Windows 10 tablet computer. Required to host remote monitoring apps and games.
**Features**	Microelectromechanical system-based piezoresistive sensor. Two buttons for power on/off and game control input. 1 MB flash-based storage for approximately 227 hours of data. 7 days use from full charge. To fully charge: 70 min.	Customisable display with clock face. Photoplethysmographic PurePulse technology heart rate sensor. 3-axis accelerometer movement detection. Memory capacity for 7 days of full data. 7 days use from full charge. To fully charge: 1–2 hours.	Intel Atom x5 processor. 4GB RAM. Bluetooth 4.0. Wi-Fi 802.11. 64GB memory storage. 5–7 hours use from full charge. To fully charge: 3 hours.
**Data collected**	Time-stamped ACT pressure data (10 Hz).	Heart rate (variable sampling frequency; 6–30 times/min), Step count (per min).	Extraction and transmission of Fizzyo sensor and Fitbit data via sync with apps. Gaming data.
**App Details**	Fizzyo app (FizzyoHub) Developed using Visual Studio for Windows 10. Bluetooth syncing of the Fizzyo ACT sensor. *Standard phase*, syncing only. *Feedback phase*, daily and monthly breath count graphs enabled. *Gaming phase,* games (developed in Unity, hosted in Microsoft store) able to be installed and played.	Fitbit app (for Windows 10) Developed by Fitbit Inc. Bluetooth syncing of the Alta HR. Patient facing dashboard displaying daily and historical graphs of step and activity patterns. Feedback on progress against daily and longer-term goals.	Windows store app Required to install and update Fitbit app and Fizzyo app and ACT games.

ACT, airway clearance technique; app, Computer application.

**Figure 2 F2:**
[figure not shown]
Project Fizzyo data collection pathway. Remote monitoring sensors (Fizzyo sensor, Fitbit) connect via Bluetooth to sync data with device-specific apps on a study tablet. Anonymous data is sent to the Fizzyo cloud (either directly or via the application programming interface from the Fitbit cloud) and then linked with de-identified clinical records in the Great Ormond Street Hospital Digital Research Environment. ACT, airway clearance technique.

At recruitment, baseline assessments of lung function (spirometry: FEV_1_, forced vital capacity, forced expiratory flow_25–75_) and exercise capacity (10 metre modified shuttle walk test, with a Polar H10 heart rate monitor and Fitbit) were undertaken. A quality of life questionnaire (Revised CF Questionnaire; CFQ-R) and a physiotherapy questionnaire was completed by participants with a member of the study team digitally via REDCap. Spirometry is always performed prior to exercise capacity assessment or after at least 1 hour of rest following maximal exertion. All tests are carried out in accordance with the appropriate guidelines. These measurements were repeated midway (7–9 months) and will be collected again at the end of the study (16 months, estimated completed in December 2020). Assessments are carried out on days when participants have a clinic appointment or routine hospital admission (but not during an exacerbation).

Data are pseudonymised, stored and analysed in the secure GOSH Digital Research Environment (DRE, Aridhia, Edinburgh, UK). The DRE is a cloud-enabled, dedicated GOSH secondary use datastore of medical data from electronic patient records, remote monitoring sensors and external databases. Embedded analytic tools will enable approved researchers to perform statistical analysis within the DRE. Data encryption and transfer protocols and data sharing and processing agreements ensure data are processed in a responsible, lawful, secure and confidential way presented with NHS information governance standards, the UK data protection act (2018) and the EU GDPR (2018).

### Remote monitoring

#### Activity tracker

A Fitbit activity tracker was chosen as Fitbit allow developers to use an application programming interface (API) for extraction of processed granular heart rate and step count data. The specific activity tracker model, the Fitbit Alta HR (released in 2017), was chosen with input from CYPwCF and their families at GOSH, from a range of Fitbit devices. It is an appropriate size for the wrists of children from 6 years old and is simple to use.

The Fitbit has a photoplethysmographic heart rate sensor for heart rate measurement, which is essential to physiologically quantify adherence to recommended minutes in daily moderate to vigorous physical activity (MVPA). Heart rate data are collected continuously with a variable sampling frequency (table 1) whenever the Fitbit is worn during the 16 months. Participants are asked to wear the Fitbit during all waking hours except when bathing/swimming (it is not waterproof), and to sync data daily via Bluetooth using the Fitbit app, or at a minimum once per week: the memory capacity of the tracker. Participants are asked to charge the battery at least once per week or when notified by the device/app.

The standard Fitbit app provides feedback data, which is available for participants to view throughout the study. After participants sync their device, the study team extract anonymised data from the Fitbit cloud using the API. It is downloaded to the Fizzyo data cloud and then transferred securely into the DRE (figure 2).

#### ACT sensor

A bespoke wireless sensor was developed for Project Fizzyo with involvement from CYPwCF and their families at GOSH, physiotherapy specialists and product design specialists. The sensor is battery powered and clips on to compatible ACT devices (figure 3) in the same way that pressure manometers are clipped in during ACT training or use. It measures air pressure changes inside the physiotherapy ACT device during breathing.

**Figure 3 F3:**
[figure not shown]
Fizzyo sensor and connectors attached to four airway clearance devices. Left are oscillatory PEP devices: an Acapella choice (labelled) and Aerobika. Right shows non-oscillatory PEP devices the Pari PEP (top) and AstraTech PEP (with a mask). Breath pressure changes within the airway clearance device are recorded by the sensor. PEP, positive expiratory pressure. ACT, airway clearance technique.

Participants are instructed to use the sensor to record all ACT treatments during the study. To reduce the chance of data loss, participants are asked to sync data once per day using the Fizzyo app and charge the sensor at least once per week. Pressure data are stored on the sensor’s encrypted memory chip (capacity 1 Mb) and can be synchronised either immediately after treatment or stored to sync at a later time. Immediately upon syncing data to the Fizzyo cloud (figure 2) basic breath count processing occurs, to provide breath count feedback to participants within a few seconds (during the feedback phase of the study only). Detailed breath count analysis will be performed on cleaned pseudonymised data in the DRE.

#### ACT-driven gaming

Windows-compatible games have been developed using a bespoke structured gaming framework (https://github.com/Fizzyo/FizzyoFramework-Unity) in Unity (Unity Technologies, San Francisco, USA), through collaboration with Microsoft, UCL and Abertay University students and CYPwCF at GOSH. The framework takes real-time inputs during ACT treatments (expiratory pressure during breathing and a button press) from the Fizzyo sensor, and uses these to simulate standard joystick inputs.

Five bespoke games with different mechanics are available to participants (including Qubi, Archipelayo and Egg Toss); including gamification features such as anonymous high scoreboards and achievements. Games were designed to encourage the player to blow in the prescribed breath length and pressure range (slightly extended expiration, 15–20 cmH_2_O), typically in multiple cycles of 8–10 breath sets with pauses for huff/cough. The number of breaths and cycles in the game can be altered by the player, reflecting the personalised ACT prescriptions of children in the study. Gaming is optional for participants during ACTs, but whether games are played or not, can be identified, including which games are played during specific sessions.

#### Participant questionnaires

Physiotherapy prescription including: ACT device(s), number of breaths and sets per day, estimated duration of ACT, exercise prescription and self-reported routine physical activities for individuals are collected by participant questionnaires at recruitment, mid-point and study end. An age-specific CF questionnaire (CFQ-R: 6–11years, 12–13 years or 14years+) is also administered at these timepoints for all participants. A parental CFQ-R is completed for children under 14 years of age. The CFQ-R is a CF-specific measure of quality of life, with domains including respiratory and gastrointestinal symptoms, treatment burden and daily functioning; it is currently the best validated CF-specific patient-reported outcome measure.^12^

### Clinical data

GOSH clinical data are extracted from electronic patient records (EPIC Systems, Wisconsin, USA), pseudonymised and uploaded directly to the DRE. Historical data from older patient record systems (that are not available in electronic patient records) will be extracted, pseudonymised and uploaded to the DRE separately. Where possible, this dataset will contain a participant’s entire clinical record including physiotherapy and known key features for CF recorded in the UK CF Registry,^13^ such as genotype, anthropometry, medications, hospital admissions, lung function, pancreatic status, microbiology, co-morbidities, ACT prescription (including documented changes to technique) and exercise test results.

At RLH and RBH electronic patient records are not currently available and clinical information, including demographics and ACT prescription will be extracted from clinical records and databases. Data will be pseudonymised at source, and transferred by secure file transfer protocol to the DRE.

A clinical data processing pipeline will be developed to summarise features describing patient demographics and clinical status as frequencies (eg, number of hospital admissions) or rates (eg, number of hospital admissions per year).

### Data analysis

#### Adherence to physiotherapy

The primary outcome measures are: adherence to a participant’s daily ACT prescription (during different study phases: standard, feedback, gaming), and adherence to daily physical activity recommendations. ACT sensor (breath pressure) and Fitbit (heart rate, step count) data are processed via a data pipeline in R,^14^ within the DRE to describe these outcomes. Clinical data outcomes will be used to investigate any relationship between physiotherapy adherence and specific clinical profiles.

Adherence to medical treatment is the extent to which a patient follows the recommendations agreed upon with health professionals.^15^ As physiotherapists give personalised ACT prescriptions of varying breath count, set count and treatment session number per day, personalised adherence scores will be calculated. Daily ACT adherence will be quantified by the number and type of breaths recorded in a treatment session and per day. Cumulative, aggregate and weekly average scores will also be calculated. Adherence to the prescribed breath count (proportion of completed breaths against prescribed breaths per treatment; usually around 100 breaths), prescribed breath pressures (proportion of ideal breath pressure breaths (15–20 cmH_2_O) per treatment) and prescribed breath length (proportion of expiratory breaths at ideal length of at least 1–2 sec) and also the presence of gaps for huff and cough between sets will be assessed. A composite adherence score based on these parameters combined per session, per day and per week will be calculated.

WHO guidelines recommend that all *children and youth aged 5–17 years should accumulate at least 60 min of MVPA daily*.^16^ Adherence will be measured against this target for all participants. Time in MVPA is calculated daily as time where heart rate is greater than a personalised threshold value (usually around 120 beats/min), which will consider an individual’s resting heart rate, and maximal heart rate from the exercise test. A number of published approaches,^17^ are being investigated to determine the optimal MVPA heart rate threshold as no clear approach currently exists in the literature for the study population. Step count data will be used to support heart rate data and assist with identification of sedentary time (for resting heart rate calculation) but will not be the primary method for activity estimation as some activities do not generate a high step frequency despite being vigorous activities (eg, cycling).

#### Data processing pipeline

A data processing pipeline enabling large amounts of remotely monitored sensor data to be processed efficiently, reliably and reproducibly was developed in collaboration with Microsoft computer and data science engineers. It was developed using preliminary data collected in the first 3 months of data collection (September to December 2018) and then tested on a larger dataset (to April 2019).

The pipeline ensures data are processed consistently and data validation checks at each stage alert to errors. The pipeline is being refined throughout the ongoing data collection period but, briefly, it processes data through three main steps: *data cleaning* to remove errors, *data labelling* to mark and measure predefined constructs from raw data (eg, distinct breaths from pressure traces) and finally *data featurisation*, the quantification of variables for cluster analysis. These steps and the main features for analysis are summarised in table 2.

**Table 2 T2:** Data pipeline stages and features for cluster analysis

Sensor type of data	Data pipeline step			
	Cleaning	Labelling (of)	Featurisation of variables for cluster analysis	
			Descriptive	Describing adherence*
**ACT Sensor** Pressure–Time	Removal of blank, duplicate and non-physiological values. Any non-linear baseline drift corrected, using a sparsity based de-noising approach.^19^	Treatment sessions Pressure peaks Breaths Breaks between breaths Sets of breaths	If any breaths recorded on a day Y/N Breath count† Breath length† Breath peak pressure† Treatment duration† Number of treatments per day Number of sets in a treatment† Number of breaths per set†	Adherence score (proportion of days with any breaths recorded per total number of days) Breath count adherence (proportion of completed breaths against prescribed breaths per treatment) Set adherence (proportion of sets against prescribed sets per treatment) Treatment session adherence (proportion of completed treatments against prescribed treatments) Pressure adherence (proportion of ideal expiratory pressure breaths per treatment) Breath length adherence (proportion of expiratory breaths at ideal length per treatment)
**Fitbit** Heart rate and step count	Removal of erroneous or non-physiological data (caused by improper wearing, depleted battery, full memory capacity due to infrequent syncing). Heart rate sampling frequency made consistent (per min) using a rolling average	Gaps in data Wear time (from heart rate data) Awake wear time Time in MVPA using personalised heart rate cut-off value^17^ Points crossing MVPA cut-off value	Heart rate Resting^20^ Peak Density and variability MVPA threshold switches Step count Daily step count Density and variability Active minutes (greater than a threshold value) Combined Active minutes both heart rate and step count. Step count during periods of MVPA	Daily time in MVPA compared with 60 daily minutes recommended. Weekly time in MVPA, 7 day window compared with 420 weekly minutes recommended.

Not all features shown.

*Features quantified as adherence per prescribed treatment session, per day, per rolling 7 day week, or other time point as required for analysis. ACT prescription is taken from clinical records and physiotherapy questionnaires.

†Total and/or average per treatment, SD, min, max values.

ACT, airway clearance technique; MPVA, moderate to vigorous physical activity.

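### Whole-phase contrasts in ACT adherence can move with the prescription as well as with behaviour, so repeat them on a recruitment-fixed denominator and on raw counts

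*Protocol article*

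**What the plan says.** Under Adherence to physiotherapy, the article names as a primary outcome "adherence to a participant’s daily ACT prescription (during different study phases: standard, feedback, gaming"). It defines adherence as "the extent to which a patient follows the recommendations agreed upon with health professionals". Breath-count adherence is the "proportion of completed breaths against prescribed breaths per treatment; usually around 100 breaths".

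Table 2 (Data processing pipeline) adds "Set adherence (proportion of sets against prescribed sets per treatment") and "Treatment session adherence (proportion of completed treatments against prescribed treatments"). Its footnote gives the source of the denominator: "ACT prescription is taken from clinical records and physiotherapy questionnaires".

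Three other sections bear on whether that denominator stays still:

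- Study design says that clinical prescriptions carry on as usual through the 16 months.
- Participant questionnaires says that the prescription items, including breaths and sets per day, "for individuals are collected by participant questionnaires at recruitment, mid-point and study end". Data collection places the mid-point at months 7–9 and the end at month 16.
- Clinical data lists among the items to extract "ACT prescription (including documented changes to technique").

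Statistical analysis then plans to quantify change in adherence to prescriptions over time and with gaming or feedback, and to relate adherence clusters to health outcomes.

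**The concern.** A ratio of completed to prescribed treatment changes when either part changes. The design compares each child with himself or herself across standard, feedback, gaming and removal periods. Every child follows the same sequence, and no concurrent group without the interventions is described. If prescriptions are revised during the 16 months, the ratio can rise or fall while the child does exactly what he or she did before, and a phase comparison would credit or debit that to feedback or gaming.

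The same applies to aim 2, the association of adherence with clinical outcomes. If prescriptions are altered as a child's health alters, the ratio carries information about clinical status through its denominator. An association with lung function or admissions then does not reflect behaviour alone.

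**Working it through.** The article states no figure for this quantity, so there is none to reproduce. The check is a timeline, a count of the affected features, and ratio arithmetic.

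**1. Timeline** (Study design, Data collection, Participant questionnaires)

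| Months | Condition | Prescription questionnaire |
|---|---|---|
| 0–2 | Standard | Recruitment |
| 2–4 | Feedback | None |
| 4–12 | Feedback and gaming | Months 7–9 |
| 12–14 | Feedback, gaming removed | None |
| 14–16 | Both removed | Month 16, at the end |

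The only questionnaire update between recruitment and the final visit falls inside the gaming phase. None falls on a phase boundary (months 2, 4, 12, 14).

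**2. Features affected.** Table 2 lists six ACT adherence features. Three divide by a prescribed number: breath count, set and session. Three do not: days with any breaths, pressure and breath length. The composite is affected through breath count.

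**3. One child, behaviour constant.** Adherence = completed / prescribed. The article gives about 100 prescribed breaths as usual. The 70 completed, and the revised prescriptions of 80 and 120, are assumptions.

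- 70/100 = 70.0%
- 70/80 = 87.5%
- 70/120 = 58.3%
- Sessions, at one completed per day: 1/2 = 50% and 1/1 = 100%

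**4. Cohort mean.** If a share q of children changes prescription and nobody changes behaviour, shift = q × (new ratio − old ratio).

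| q (assumed) | 100 to 80 breaths | 100 to 120 breaths | 2 to 1 sessions |
|---|---|---|---|
| 10% | +1.75 points | −1.2 | +5 |
| 20% | +3.5 | −2.3 | +10 |
| 30% | +5.25 | −3.5 | +15 |

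For example, 0.20 × (0.875 − 0.700) = 0.035, or 3.5 points.

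**5. Where the shift lands.** Suppose the new value comes from the mid-point questionnaire and applies forward from that visit.

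- Months 0–4: no shift.
- Gaming phase (8 months): the updated share is (12 − 9)/8 = 0.375 to (12 − 7)/8 = 0.625. The whole-phase mean moves by 0.375 × 3.5 = 1.3 to 0.625 × 3.5 = 2.2 points.
- Months 12–16: the full 3.5 points.

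The artefact therefore enters standard versus gaming and standard versus after removal. It does not enter the steps at the phase boundaries.

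**6. The proposed repeats.** With the recruitment denominator the ratio is 70/100 before and after, a shift of 0. Raw counts are 70 before and after, also a shift of 0.

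**The case against.** Most of the opposing case narrows the point, and these parts of it stand:

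- **The denominator follows the definition.** Adherence is defined against what was agreed with health professionals. If the target rises and the child does not follow, the child is less adherent in that sense. A current-prescription denominator is not an error.
- **A rule for merging the two sources may exist elsewhere.** This is a condensed article, and an order of precedence or effective date could sit in a fuller document. Its absence here is not the finding.
- **Change in prescribed numbers is inferred.** Clinical data speaks of changes to technique, and carrying on as usual could be read as unchanged. Against that, breaths and sets are collected three times, and usual care is nowhere said to be frozen.
- **Questionnaire updates miss the phase boundaries.** If applied forward, they do not disturb the steps at months 2, 4, 12 and 14. Whole-phase and before/after contrasts remain exposed.
- **Denominator-free measures are already derived.** Table 2 includes breath counts, treatments per day and days with any breaths. However, Statistical analysis frames the phase comparison as change in adherence to prescriptions or recommendations and does not name these measures for it.

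Two stronger readings are tempting. One is that children who see daily breath counts come to report what they do as what was prescribed, so that the intervention itself distorts the denominator. The documents do not establish this: the questionnaire is completed with a member of the study team, clinical records are also a source, and nothing shows such drift. The other is to set one child's 80/80 = 100% beside 80/120 = 66.7% and call the gap the size of the bias. Those are opposite hypotheticals, not a phase contrast.

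**Conclusion.** The point holds in a limited form. Current-prescription adherence is a sound description, but its change between whole phases, and its association with clinical outcomes, cannot be read as behaviour alone when the prescription may change during follow-up and no concurrent control is described.

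The size is unknown, because the article gives neither the frequency nor the direction of prescription changes. Under the assumed scenarios with 10–30% of children changing, the cohort mean shifts by about 1 to 5 points in either direction for breath count, and by 5 to 15 points if the change is from two sessions to one. These figures assume constant behaviour and a revision in one direction; offsetting revisions would shrink them. The documents do not support saying that the outcome is wrongly defined or that the phase-boundary steps are biased by the questionnaire updates.

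**What to change.** Keep adherence to the current prescription as the defined outcome. State that the denominator on each day is the dated clinical record where one exists and the questionnaire otherwise.

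Repeat every phase contrast in two further ways:

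- (a) with the denominator held at the recruitment prescription;
- (b) on raw breaths and treatments per day, which Table 2 already derives.

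Where a change appears only in the current-prescription ratio, report it as possibly reflecting a change of prescription rather than an effect of feedback or gaming. This guides interpretation; it is not a rule that all versions must agree before a phase effect is reported.

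The cost is one sentence on sources and two extra summaries from existing features, with no new data and no change to care. The small downside is that recruitment-fixed adherence is less current for children whose prescription truly changed, which is why it accompanies the defined outcome and does not replace it.
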